**Methods/design::**

In this study, we will use our own front-to-back clinical research method. We plan to include 120 young and middle-aged female patients who meet the diagnostic criteria for HS. The untreated HS of the enrolled patients will be used as blank controls. The intervention group will be given acupuncture treatment. The assessment of scar area, color, hardness, thickness, itching and pain will be recorded for 30 days of treatment.

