### Interventions

2.3

The participants included in the observation will be self-controlled, and each patient randomly selected 3 different scar treatment areas at the same site as observation specimens.

Control group: Take the untreated pathological scars of the participants as blank control. This group will not give any intervention.

Intervention group: Before the treatment, we will carry out strict physical examination and dermatological examination on the patient, and make sure that the patient has no obvious contraindications, and then carry out acupuncture treatment.

(1)Patient position: Choose according to the patient's scar location (supine position, lateral position or sitting position, etc.).(2)Operation steps: first disinfect the scar area and perform acupuncture in a circular shape on the local scar area of the patient. Needle retention time is 30 min, and the needle is moved twice during the needle retention process. The number of acupuncture depends on the size of the scar area of the affected area, with a minimum of 4 and a maximum of 15, each needle is about 3 cm apart, and the needle insertion is 1 cm to 1.5 cm. At the end of the 30-minute needle retention time, hold the hand on the eye of the needle with a medical swab and proceed in sequence.(3)Course of treatment: once every two days, 30 days as a course of treatment. Observe the scars every 15 days of treatment (Fig. 2).

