### Sample size calculation

2.5

The sample size for this trial is based on an expected mean difference between groups of 11 points of the Constant–Murley questionnaire, which is the minimum clinically important difference. To detect this difference between both treatments, with a value of a = 0.05 (probability of committing a type I error) and a statistical power of 95%, a minimum of 49 patients per group is needed. This minimal sample size estimate has been increased by 20% after considering the potential dropouts, finally including 60 patients for each group. Accordingly, the proposed experimental hypothesis is that there will be a difference of at least 11 points in the Constant—Murley questionnaire in the intervention group versus the control group. The sample size was determined using the Stata SE software.

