### Randomization and blinding

2.6

(1)The concealment of random schemes: After the scheme design is completed, the random schemes are enclosed in a sequence-encoded, sealed, light-tight envelope. Then it is handed over to the person in charge of the subject, after screening qualified cases, the envelope is opened to determine the grouping.(2)The recorder fills in the case report form with basic data and observation of the patient's local and systemic symptoms.(3)Unified production of various documents.(4)Check and confirm the correctness and completeness of all research data records and reports and case report forms, and ensure consistency with original data.

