### Statistical analysis

2.7

Data management uses EXCEL software to build a database, double entry, check for outstanding values, and lock. Statistical analysis will be performed using SPSS 25.0 software for statistical analysis. The normality of the measurement data is tested. The data obeying the normal distribution is Student's *t* test, which is expressed by mean ± standard deviation. The data not obeying the normal distribution is rank sum test. And marginal homogeneity test; count data are expressed by rate and composition ratio, and comparison is performed by chi-square test; repeated measurement data are expressed by mean ± standard deviation, intra-group comparison is performed by analysis of variance of repeated measurement data, and inter-group comparison is by multivariate analysis of variance (MANOVA). *P* ≤ .05 indicates that the difference is statistically significant.

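### The between-group tests in section 2.7 (MANOVA, chi-square) assume independent units, but section 2.3 describes a self-controlled design with three scar areas per patient

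*Protocol article*

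**What the plan says.** Section 2.7 (Statistical analysis) names Student's t test for normally distributed data. Otherwise, "The data not obeying the normal distribution is rank sum test". It mentions the marginal homogeneity test without giving it a use, and compares count data by chi-square. For repeated measurements, the within-group comparison is a repeated-measures analysis of variance and "inter-group comparison is by multivariate analysis of variance (MANOVA"). It does not say whether the t or rank sum test is paired.

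Section 2.3 (Interventions) describes the units to be compared. Every woman acts as her own control: "each patient randomly selected 3 different scar treatment areas at the same site". The control arm is defined in the same section: "Take the untreated pathological scars of the participants as blank control". The abstract agrees with a within-patient comparison: "we will use our own front-to-back clinical research method".

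Two other sections point to parallel groups. Section 2.5 (Sample size calculation) ends with "finally including 60 patients for each group", and section 2.6 (Randomization and blinding) says that "after screening qualified cases, the envelope is opened to determine the grouping".

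**The concern.** Under section 2.3, the treated and untreated scars sit on the same women. A patient with a severe scar will tend to score high in both conditions, so the two sets of scores are correlated. MANOVA between groups and the chi-square test take the two sets as coming from different, independent units. Followed as written, they attach the wrong standard error to the treatment difference.

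The three areas per patient add a second layer of correlation. Section 2.7 does not say whether they are averaged, modelled or entered as separate observations.

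The between-group P values for the Vancouver-based total score (section 2.4.1) and for the response classes (section 2.4.2) depend on these choices.

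**Working it through.** **The plan's own figure.** The article gives no error rate to reproduce. Its nearest figure is 49 per group, raised to 60. The independent two-group formula is n = 2[SD(1.96 + 1.645)/11]². No SD is stated. With an assumed SD of 15 it gives 2(15 × 3.605/11)² = 48.3, so 49. The 20% increase gives 49 × 1.2 = 58.8, or 49/0.8 = 61.25, either side of the stated 60. The sample size therefore fits an independent two-group calculation, not a paired one.

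**Inputs.** From the document: alpha 0.05, 60 per group, three areas per patient, visits at days 15, 30, 45 and 60. Assumed: within-patient correlation ρ of 0.5 to 0.7, equal variances, two-sided testing.

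**Reading A: self-controlled (section 2.3).** With one area per condition, the true variance of the mean difference is 2σ²(1 − ρ)/n, while an unpaired test uses 2σ²/n.
- Ratio of unpaired to true SE = 1/√(1 − ρ): 1.41 at 0.5 and 1.83 at 0.7.
- True alpha = 2[1 − Φ(1.96/√(1 − ρ))]: 0.0056 at 0.5 and 0.0003 at 0.7.

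Several areas per condition do not change this if all areas of a patient share one correlation. For three areas in each condition, the variance factor relative to the naive test is 1 + 2ρw − 3ρb, where ρw is the correlation within a condition and ρb that between conditions. Setting ρw = ρb = ρ gives 1 − ρ again. The test becomes anti-conservative only if ρw exceeds 1.5ρb.

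**Reading B: parallel groups (sections 2.5 and 2.6), three areas entered as separate units.**
- Design effect = 1 + 2ρ: 2.0 at 0.5 and 2.4 at 0.7.
- True alpha = 2[1 − Φ(1.96/√(1 + 2ρ))]: 16.6% at 0.5 and 20.6% at 0.7.

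**Check by simulation, 60 per group.** For t tests (10,000 runs), Reading A gave 0.006 at 0.5 and below 0.001 at 0.7, while a paired t test held 0.051 at both. Reading B gave 0.170 and 0.201. For the two-group MANOVA over four visits (4,000 runs, assumed correlation between visits 0.6):

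| Data | True alpha, ρ = 0.5 | True alpha, ρ = 0.7 |
|---|---|---|
| Same patients in both conditions | 0.001 | about 0 |
| Parallel groups, three areas as units | 0.33 | 0.42 |

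With independent patients and one value each, the MANOVA gave 0.046, which is valid.

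**The case against.** The strongest defence is that sections 2.5 and 2.6 describe parallel groups, for which t, rank sum, chi-square and MANOVA are ordinary choices. The article is also a condensed text, so the handling of the three areas may be fixed elsewhere. If the trial is purely before-after, the within-group repeated-measures analysis already fits. This stands in part: the tests suit a parallel trial with one value per patient. But section 2.3 does not describe such a trial, and the tests that section 2.7 does name do not fit what section 2.3 describes. Silence about the areas is not in itself a fault, and the 17% to 21% applies only if they are counted as separate units.

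A reader might infer more than the document supports:
- *That false positives are inflated under the self-controlled design.* With a common correlation the test is conservative. The 17% to 21% belongs to parallel groups.
- *That repetition over visits is ignored.* Repeated-measures analysis of variance and MANOVA both allow correlated visits.
- *That incomplete patients will be deleted, losing 20% of 120 = 24.* No missing-data rule is stated, and one may sit in an analysis plan that is not shown. The allowance from 49 to 60 is 11 per group, 22 in all, and leaves the required 49.
- *That the t and rank sum tests are declared to be independent-sample tests.* The text does not say which form is meant, and the list also includes one paired test, marginal homogeneity.
- *That omitting baseline as a covariate is an error.* The efficacy index is already a change relative to baseline.

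**Conclusion.** The point holds in this form: the between-group MANOVA and the chi-square test do not match the self-controlled design of section 2.3, and the form of the t and rank sum tests is left open. Under that design, ignoring the pairing costs power: the SE is 1.41 to 1.83 times too large, and the true alpha is about 0.006 to 0.0003 instead of 0.05. Under the parallel design, counting areas as units would push the alpha of a t test to about 17% to 21%.

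Both ranges rest on an assumed correlation of 0.5 to 0.7, and the first also on one common correlation among all areas of a patient. The direction of the error cannot be settled until the design is. That is why the choice of test and the conflict between section 2.3 and sections 2.5 and 2.6 have to be resolved together.

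**What to change.** First reconcile section 2.3 with sections 2.5 and 2.6 and state one design. Then rewrite section 2.7 to match it.

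- **If self-controlled:** compare conditions within patient. Use a paired t or signed-rank test on each patient's mean over the areas in each condition. Alternatively, use a linear mixed model with patient and area-within-patient effects and a covariance across visits at least as flexible as the one MANOVA allows; random intercepts alone would be more restrictive. For the response classes, replace chi-square by McNemar's test (two classes) or the marginal homogeneity test (more than two).
- **If parallel:** reduce the three areas to one value per patient, after which the named tests are suitable, or model the clustering of areas within patients.

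Adjusting for the baseline score is an optional improvement that needs no extra data.

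The change to section 2.7 is a matter of wording, and the named software can fit the model. Settling the design is more than wording, since it also decides what the envelopes allocate and which sample size formula applies. Section 2.9 says recruitment has not started, so both can be done before any data exist.

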### Data management

2.8

Information obtained from the evaluation of each participant will be recorded on a paper print-out. The information will then be handwritten on a paper document case report form and entered into an Excel file for future statistical analyses. In accordance with the Personal Information Protection Act, the names of all participants will not be disclosed, and a unique identifier number given during the trial will be used to identify participants. All of the participants will be informed that the clinical data obtained in the trial will be stored in a computer and will be handled with confidentiality. The participants’ written consent will be stored by the principal investigator.

### Ethics

2.9

The study will be conducted under the Declaration of Helsinki principles, as well as following the norms of good clinical practice. Recruitment of patients has not started in this study. The study plan will be submitted to the ethics committee of the Second Affiliated Hospital of Shaanxi University of Chinese Medicine for review. The study protocol will be approved by the ethics committee of the Second Affiliated Hospital of Shaanxi University of Chinese Medicine. The protocol of this study has been registered in the Chinese Clinical Trial Registry with the number ChiCTR2000032624.

## Discussion

3

HS is a common disease in plastic surgery. It is a manifestation of skin connective tissue response to trauma beyond the normal range. HS often occurs after surgery, trauma and burns, which not only affects the appearance, but also can cause symptoms such as itching, pain, and even cause Severe dysfunction.^[9]^ It is a unique pathological phenomenon after the healing of human skin injury, which brings difficulties to the physical and mental recovery of patients. It is clinically found that the formation of HS is caused by abnormal proliferation of various wound healing processes.^[10]^ However, the formation mechanism of HS is not yet fully understood. It is generally believed that the formation of scars is caused by the imbalance of collagen synthesis and degradation after the body's inflammatory response. The surface layer of HS consists of several layers of epithelial cells to form a very thin and smooth covering layer, and the lower dermis layer is replaced by collagen fibers. Collagen fibers are thick and irregularly arranged, forming an arc-shaped long cord-like collagen to form a vortex-shaped histological scaffold, accompanied by a large amount of fibroblast infiltration.^[11]^ Modern medical scientists have realized through research that when the skin tissue is damaged and damaged to a certain depth, an early inflammatory waterfall-like reaction will appear on the wound surface. Leukocytes, macrophages, mast cells, etc. infiltrate, release a variety of cytokines, fibroblasts and myofibroblasts proliferate and synthesize large amounts of collagen and matrix. This caused the abnormality of collagen metabolism and structural arrangement, coupled with the influence of factors such as microcirculation and oxygen free radicals, which promoted the formation of HS.^[12]^ Sometimes the granulation tissue can be completely absorbed by the surrounding normal tissues after the inflammation factor subsides without going through the scar hyperplasia process, but sometimes it continues to hyperplasia.^[13]^ The development of HS can be divided into three periods, namely hyperplasia, decline and maturity. Scars usually begin to proliferate 1 to 3 months after wound healing, and reach a peak in 6 months. Its clinical features are local hyperemia, bright red color, and active hyperplasia, but it does not invade normal skin. After the proliferative period is the decline period, generally 6 months to 1 year. At this time, the color of the purpura gradually turns to brown, the volume becomes smaller, and the hardness becomes softer. Then enter the mature stage. The specific clinical manifestation is that the scar is obviously higher than the surrounding normal skin, and the local thickening and hardening. In the early stage, due to capillary congestion, the scar surface was red, flushed, or purple. In this period, itching and pain are the main symptoms, and this can even cause the surface to rupture due to scratching. After a certain period of time, the hyperemia of the scar area decreases, the surface color becomes lighter, the scar gradually becomes soft and flat, and the symptoms of itching pain are reduced or disappeared. The length of this hyperplasia period varies with the person and the lesion.

The most common surgical treatment for HS is surgical resection. According to research reports, the rate of HS resection alone is as high as 48% to 100%.^[14]^ However, the effect of this method on wound self-healing is almost zero, so there is still scar formation due to uncontrolled wound healing again. Therefore, surgical treatment should usually be combined with other treatment options, such as steroid injection in the scar, compression therapy, radiation therapy, etc., to prevent recurrence of purpura. In addition, the development of laser technology provides another important auxiliary means for the treatment of purpura.^[15]^ More and more lasers with different wavelengths are being put into use. The thermal effect of the tissue caused by the laser beam depends on the tissue's absorption and conversion of the laser into thermal energy. The high-frequency pulsed laser has a better prospect and is most suitable for the treatment of HS, with an effective rate of more than 57%. Cryotherapy is suitable for smaller scars. Its mechanism of action is to disturb local scar microcirculation through hypothermia, cells are hypoxic and ischemic, leading to cell necrosis, which leads to tissue necrosis and exfoliation ulceration. The effective rate of treatment can reach more than 51%, and the effective rate can be 72% if used in combination with steroid hormones.^[16]^ The side effects of cryotherapy can cause complications such as deepening of local skin pigmentation and mild to moderate skin atrophy. Currently, aesthetic physicians and scientific researchers are actively looking for natural and synthetic antagonists, which affect fibroblasts to produce scar matrix. Therefore, the search for safe, effective and convenient treatments for hypertrophic scars has been the focus of medical research and research in recent years. TCM has a definite curative effect on prevention and treatment of HS, and has unique advantages.^[17]^ Oral Chinese medicine, external application of Chinese medicine, acupuncture and integrated Chinese and Western medicine treatment can be selected. Among them, acupuncture combined with oral medication is not only effective in treating the disease, but also has high psychological acceptance. Moreover, it is safe and secure, with little toxic and side effects, and easy to operate. Acupuncture therapy is easy to learn and use, economical and easy to promote. In this study, we will use our own front-to-back clinical research methods to evaluate the clinical efficacy and related indicators of young and middle-aged female patients who meet HS, and then look for an objective and effective treatment of HS. We aim to provide an objective basis for the clinical efficacy of acupuncture treatment of HS.
